### Allocation

Allocations will be generated by an independent biostatistician, with study investigators blinded to the randomisation sequence. A 1:1 randomisation ratio to standard of care (female treatment only, *Control group*) or female partner treatment with concurrent male partner treatment (*Intervention group*), in blocks of size four-six, will be used with stratification by recruitment site and known risk factors for recurrence: intrauterine device (IUD)-use and circumcision status. After obtaining verbal consent, the research nurse will log into a password-protected online database, REDCap, an electronic data capture tool hosted and managed by Helix (Monash University) [42], to complete screening and eligibility assessments. The randomisation allocation button will only be visible once all the required information has been entered and the couple are deemed eligible. REDCap will then retrieve the next ‘sealed’ allocation from within each recruitment site and either the IUD-user or non-IUD user stratified allocation and then within these two groups, an uncircumcised or circumcised stratified allocation.

If a protocol violation occurs after randomisation (defined above), reasons will be collected and the participant will be deemed either lost to follow up or withdrawal if this is formally what they decide to do. Couples who fail screening will not be included in the evaluable population for analyses and therefore the next “sealed” allocation can be used to recruit an additional couple.

As this is an open-label RCT, both the research nurse performing randomisation and the participants will know which group they are in. However, the microscopists performing Nugent scoring, clue cell reporting and amine testing will be blinded to randomisation group.

### Study components and data collection methods

The study constitutes enrolment, day 8 post-antibiotic follow up and then three other follow-up time points. A summary of the study schedule and procedures for couples at each study time point is provided in Table 1 and Fig. 2.

**Fig. 2 Fig2:**
[figure not shown]
Summary of study schedule and procedures for women and men at each time point

#### Baseline procedures

Once eligibility has been assessed and consent forms signed, participants will be instructed on self-collection of high-vaginal swabs and vaginal secretions on a slide for NS, penile swabs, and urine samples (Table 1, Fig. 2), and provided with a baseline questionnaire. A clinician and pharmacist will instruct participants about antibiotic use and AEs. Couples will be asked to avoid alcohol and to abstain from sex during treatment.

#### Home and clinic follow up

Female participants will collect samples and complete questionnaires on four occasions after baseline including the day after completing antibiotics (day 8), and at weeks 4, 8 and 12 (Table 1, Fig. 2). At scheduled clinic visits (weeks 4 and 12) females will be assessed for BV by Amsel and Nugent criteria, and will complete a questionnaire. At day 8 and week 8, swabs, slides for Nugent scoring, and questionnaires completed at home will be returned by replied paid post to MSHC. If a woman returns a home slide with NS = 7–10, or reports symptoms indicating BV, she will be booked for an interim clinic visit and assessed for BV. All slides collected at home or in non-MSHC clinics will be sent via post to MSHC for scoring within a week. Slides with morphotypes unable to be easily scored will be read by a second independent microscopist and consensus reached.

Male participants will self-sample and complete questionnaires at enrolment and, for those in the *Intervention group*, the day after completing treatment (day 8), or if in the *Control group*, the day after their partner has finished her treatment (Fig. 2). Men will be instructed to complete their follow up specimens and questionnaires at the same time as their partner. All male questionnaires and specimens will be collected at home and returned by replied paid post to MSHC.

Validated questionnaires at each time point will collect data detailing sexual practices (e.g. frequency and types of sex, condom use, change in partnerships), contraceptive use, menstrual dates, genital symptoms, and any interim treatments. Adherence and AEs will be recorded on day 8 questionnaires and participants instructed to call the dedicated study phone if they have any enquiries or are concerned about any AEs experienced.

A reminder SMS will precede each scheduled self-collection time point and reminders sent for up to 2 weeks if samples are not returned, after which a participant will be classified as a non-responder for that interval, but contacted at the next follow-up point. A reminder SMS will be sent to participants 1–2 business days prior to any clinic-based appointment. All couples will receive a $10AUD voucher for each completed stage of follow-up.

#### Study endpoint visit (week 12 or BV recurrence)

The study endpoint is BV recurrence/no BV recurrence within 12 weeks of enrolment. All female participants will be asked to attend a study site for an endpoint clinic visit at week 12, or earlier, if they experience BV recurrence NS = 7–10 on self-collected swab. At the week 12 visit, the research nurse or treating clinician will assess the women for clinical signs of BV using Amsel criteria and take a swab for future molecular studies and slide for Nugent scoring (Table 1) and the participant will be asked to complete the week 12 questionnaire.

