### Outcome measures

The primary outcome is BV recurrence using current gold standard diagnostic methods defined as ≥3 Amsel criteria and Nugent score (NS) = 4–10 within 12 weeks of enrolment. The secondary outcomes are i) BV recurrence defined as NS ≥ 7 within 12 weeks, ii) BV recurrence defined as ≥3 Amsel criteria within 4 weeks, iii) BV recurrence defined as NS ≥ 7 within 4 weeks, iv) recurrence of a microbiota dominated by BV-associated bacteria within 12 weeks, and v) recurrence of a microbiota dominated by BV-associated bacteria within 4 weeks. All Amsel criteria endpoints require a clinic visit whereas Nugent endpoints can be evaluated using specimens collected at home (see Table 1). Additional measured outcomes include i) adherence to antibiotic therapy (by both women and men), ii) acceptability of antibiotic therapy to men, and iii) adverse effects (AEs) in men (safety analysis).

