#### Treatment of BV recurrence

All women experiencing BV recurrence during the study or at its conclusion will be given an appointment with a clinician and offered treatment accordingly. Couples randomised to the *Control group* will be offered the opportunity for male partner treatment if the female experiences BV recurrence during the study. These data will not be included in the trial but will contribute to a subsequent sub study.

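### The protocol conflicts on whether a home swab with Nugent score 7–10 triggers an interim check or the endpoint visit, so primary follow-up may close early for women who do not meet the primary definition

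*Protocol article*

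**What the plan says.** Four places in the protocol article bear on this.

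- *Outcome measures* defines the primary outcome as recurrence "defined as ≥3 Amsel criteria and Nugent score (NS) = 4–10 within 12 weeks of enrolment". *BV diagnosis methods* uses the same two-part definition for the trial's diagnosis of BV. A Nugent-only outcome, "BV recurrence defined as NS ≥ 7 within 12 weeks", is listed as secondary. The section adds: "All Amsel criteria endpoints require a clinic visit whereas Nugent endpoints can be evaluated using specimens collected at home".
- *Home and clinic follow up* says of the home samples: "If a woman returns a home slide with NS = 7–10, or reports symptoms indicating BV, she will be booked for an interim clinic visit". There she is assessed for BV. Home slides are due at day 8 and week 8; clinic visits are due at weeks 4 and 12.
- *Study endpoint visit (week 12 or BV recurrence)* has all women "asked to attend a study site for an endpoint clinic visit at week 12, or earlier", the earlier date applying "or earlier, if they experience BV recurrence NS = 7–10 on self-collected swab".
- *Treatment of BV recurrence* attaches further steps to BV recurrence, including an offer of partner treatment to control couples, without saying which definition is meant. It ends: "These data will not be included in the trial but will contribute to a subsequent sub study".

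*Statistical methods* specifies an unadjusted Cox comparison and keeps women seen at week 4 but not at week 12.

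**The concern.** One swab result has two consequences in the text. In one section it is a signal that prompts a clinical check. In the next it is itself named recurrence, and the visit it prompts takes the place of the week-12 endpoint visit. The two agree when the woman meets the primary definition at that visit. They part when her home Nugent score is 7–10 but she has fewer than three Amsel criteria in clinic: an interim visit implies that she carries on, an endpoint visit implies that she has finished.

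If a site follows the second reading, her primary follow-up stops before week 12. In a Cox analysis she is censored at that visit. The Nugent score that led to the censoring is one of the two components of the primary outcome, so the censoring is plausibly informative, and a primary event between that visit and week 12 would go unseen. After a positive day-8 swab, even the week-4 assessment could be lost.

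**Working it through.** **The texts side by side**

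| Question | *Home and clinic follow up* | *Study endpoint visit* |
|---|---|---|
| Trigger | Home Nugent score 7–10, or symptoms | Home Nugent score 7–10 only |
| Name given to the trigger | None | BV recurrence |
| Status of the visit | Interim | Endpoint, in place of week 12 |
| If the primary definition is not met there | Not stated | Not stated |

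The trigger in the right-hand column has no Amsel element. It matches the secondary outcome, not the primary.

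**The plan's own sample size**

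Inputs from *Sample size*: 40% against 24%, two-sided 5%, 80% power, 145 per arm, 15% loss. The mean risk is p̄ = 0.32.

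- n = (1.960·√(2·0.32·0.68) + 0.8416·√(0.40·0.60 + 0.24·0.76))² / 0.16² = 3.3855/0.0256 = 132.2, so 133 per arm without continuity correction.
- With continuity correction: (132.2/4)·(1 + √(1 + 4/(132.2·0.16)))² = 144.5, so 145. This matches the plan.
- 145/0.85 = 170.6, so 171 per arm; 290/0.85 = 341.2, so 342. Both match.

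The sample size is not in dispute. It fixes the starting point below.

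**Power if later events are missed**

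Power = Φ[(d√n − 1.960·√(2p̄(1−p̄))) / √(p₁(1−p₁) + p₂(1−p₂))], with n = 145, no continuity correction, and d = p₁ − p₂.

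- 40% against 24%: (0.16·12.042 − 1.960·0.6597)/0.6499 = 0.975, power 83.5%.
- 35% against 21%: (0.14·12.042 − 1.960·0.6350)/0.6272 = 0.704, power 75.9%.

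The documents do not say how many women have a home score of 7–10 but do not meet the primary definition in clinic, nor how many of those would meet it later. Both are assumed: 2%, 5% or 10% of control women are stopped early, and 25% or 50% of them would have had a primary event by week 12. Missed events in the intervention arm are set at 0.6 times those in the control arm.

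| Controls stopped | Share with a later event | Missed, control / intervention (points) | Observed risks | Power |
|---|---|---|---|---|
| 2% | 25% | 0.5 / 0.3 | 39.5% / 23.7% | 82.8% |
| 2% | 50% | 1.0 / 0.6 | 39.0% / 23.4% | 82.1% |
| 5% | 25% | 1.25 / 0.75 | 38.75% / 23.25% | 81.8% |
| 5% | 50% | 2.5 / 1.5 | 37.5% / 22.5% | 79.9% |
| 10% | 25% | 2.5 / 1.5 | 37.5% / 22.5% | 79.9% |
| 10% | 50% | 5.0 / 3.0 | 35.0% / 21.0% | 75.9% |

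Two limits apply. The factor of 0.6 holds the risk ratio at 0.60 in every row by construction (for example 21/35). The implied proportional-hazards ratio moves only from ln 0.76/ln 0.60 = 0.537 to ln 0.79/ln 0.65 = 0.547. The table therefore measures lost power and does not quantify bias from informative censoring. It also counts stopped women as non-events in a two-proportion test, whereas the planned Cox analysis would censor them.

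**The case against.** The strongest reply is that the two sections can be read together: a positive swab brings the woman in, she is assessed on the trial's two-part definition, and only confirmed BV ends follow-up. On that reading the Nugent label in the endpoint section is loose wording and no one is lost. The reading is reasonable, and no section says outright that a woman who does not meet the primary definition stops. But it has to be supplied by the reader, and the literal text gives sites a different instruction.

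A reader might infer that some women finish with no valid primary outcome. The documents do not support that. The early visit is a clinic visit at which the woman is assessed for BV, so if she attends she can be classified on that date. Having made a clinic visit, she can remain in the modified intention-to-treat set. What could be lost is her status from then until week 12.

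A reader might also take the sentence "These data will not be included in the trial but will contribute to a subsequent sub study" to exclude later data from Nugent-positive women who do not meet the primary definition. It directly follows the offer of partner treatment to control couples and most naturally refers to data arising from that. What remains is that the section does not say which definition of recurrence it uses.

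Finally, censoring rules may properly be left to the statistical analysis plan. That is fair for the analysis, but whether a woman is followed to week 12 is trial conduct. The analysis plan is to be written close to data lock and cannot restore visits that were not made.

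**Conclusion.** The conflict is in the current text and should be resolved. As written, the endpoint section may close primary follow-up early for women who have a home Nugent score of 7–10 without meeting the primary definition at the visit that follows. If it does, the censoring is plausibly informative. It would be too strong to say that the Cox assumption fails, or that the control arm certainly loses more events: the first depends on how sites act, the second on the treatment working.

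The size rests on assumption alone. Power without continuity correction goes from 83.5% to between about 83% and 76%. The lower figure is the most pessimistic combination considered, with 10% of controls stopped and half of them having a later event; the middle of the range stays near 80%. The effect is probably modest, but it is avoidable.

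**What to change.** Reconcile the sections on home and clinic follow up, the study endpoint visit and treatment of BV recurrence as follows.

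1. State that only a clinic visit with at least three Amsel criteria and a Nugent score of 4–10 closes primary follow-up. Call the visit prompted by a home swab interim in both sections, with the same trigger in each.
2. State that a woman with a home score of 7–10 who does not meet that definition remains at risk for the primary outcome and keeps her remaining scheduled samples and clinic visits, including week 12. Her swab counts for the secondary Nugent endpoint only.
3. State which definition of recurrence the treatment section refers to. No treatment rule is proposed here; the passages only need to agree.
4. Report by arm the number of women with a Nugent score of 7 or more who did not have a recurrence on the primary definition.

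The cost is small: changes of wording, one extra reported count, and week-12 visits that are already in the schedule.

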#### Treatment of BV recurrence

All women experiencing BV recurrence during the study or at its conclusion will be given an appointment with a clinician and offered treatment accordingly. Couples randomised to the *Control group* will be offered the opportunity for male partner treatment if the female experiences BV recurrence during the study. These data will not be included in the trial but will contribute to a subsequent sub study.

### Collection of genital specimens for future analysis

Genital specimens will be collected at every time point for future molecular analysis (Table 1). Vaginal swabs will be collected using a flocked swab (Copan Diagnostics, Brescia, Italy) and transferred into a vial containing AssayAssure® Multilock (Sierra Molecular, Princeton, NJ, USA) for biological sample stabilisation, preservation and storage. Men will be instructed to retract their foreskin (if applicable) and swab a flocked swab (Copan Diagnostics) pre-moistened with sterile water around the coronal sulcus and over the glans of the penis, prior to transferring into a vial containing AssayAssure® Multilock. In addition, men will be instructed to urinate approximately 20 ml of urine into a standard urine pot. They will be provided with a transfer pipette to then transfer 15 ml into a vial containing urine preserving agent, AssayAssure® Genelock (Sierra Molecular). All specimens will be collected in clinic or sent via post to the Central Co-ordinating site, processed and then stored at -80C for future analysis.

### Statistical methods

Analysis and reporting of the trial will be in accordance with the Consolidated Standard of Reporting Trials (CONSORT) guidelines. A detailed Statistical Analysis Plan will be written close to final data lock, but before any analyses are performed, that will define all analyses in detail. Enrolment and longitudinal specimen and questionnaire data will be entered into two separate password-protected online databases within REDCap and then imported into a statistical package (Stata) for analysis.

The Primary Analysis is a mITT analysis. All randomised women will be analysed as randomised if they 1) returned for ≥1 clinical visit, 2) took one or more doses of antimicrobial therapy, and 3) are part of the evaluable population. Sensitivity analyses will include analyses that take into consideration adherence to treatment (for women and/or men). Women who attend at week 4 but not week 12, are still eligible for the primary outcome analysis. Primary analyses will be simple unadjusted two-group comparisons of the randomised arms using Cox regression. If there are important imbalances in baseline characteristics, further adjusted analyses will be performed. Cox regression analyses will be also used to assess co-variates associated with recurrence including demographics, sexual practices, contraception use, smoking and other factors previously shown to be associated with BV recurrence.

Secondary analyses include a per protocol analysis for participants qualifying for the mITT population and who adhered to ≥70% of doses of the medication(s) prescribed (i.e. ≥10 doses of a 14-dose prescription or ≥ 5 doses of a 7-dose prescription). Any AEs leading to cessation of treatment, and all reported clinical AEs will be summarised descriptively. This will include every male who took ≥1 dose of at least one of the investigational drugs.

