Evidence that sexual transmission contributes to the pathogenesis of BV has been reported since the 1950s, and led to six male partner treatment trials in the 1980s and 90s [10, 11]. Treatment regimens for males in these trials differed and included oral metronidazole (2 g single dose, 2 g on days 1 and 3 or 500 mg twice daily [BID] 7 days), single dose oral tinidazole (2 g), or oral clindamycin (150 mg four times a day [QID] 7 days) [12–17], with a number of non-standard regimens with respect to current practice. Women were treated with similar regimens to their partner. Only one trial demonstrated a significant impact of partner treatment on recurrence (men received oral metronidazole 2 g single dose vs placebo) [14], and as a consequence, partner treatment was not adopted in clinical practice [10, 18, 19]. However, reviews of the early partner treatment trials also highlighted the significant issues that render their findings inconclusive [10, 18, 19]. Since the publication of these partner-treatment trials, an increasing body of epidemiological data shows women with a regular partner are more likely to experience post-treatment recurrence compared to women with no partner or a new post-treatment partner [8, 20, 21], and microbiological data supports transmission or exchange of BV-associated bacteria (henceforth referred to as BV-organisms) during sexual activity [22–27]. Notably, BV-organisms are more prevalent in the sub-preputial space (under the foreskin) and distal urethra of male partners of females with BV than without BV [22, 26], and recently, the composition of the meatal microbiota was shown to be particularly predictive of incident BV in female partners [24]. A biofilm dominated by BV-organisms has also been detected in male urine and semen more commonly in male partners of females with BV than without BV [28]. Both sexual activity and male circumcision have been shown to influence the penile microbiota [23, 29, 30], with male circumcision prospectively associated with a significant reduction in BV-organisms and a reduction of BV in their female partners [30–32]. Women with a circumcised partner can still develop BV [33] indicating that the sub-preputial space is not the only reservoir of BV-organisms. Collectively this body of evidence suggests that carriage of BV-organisms at both urethral and penile skin sites in men is providing a reservoir from which BV-organisms can be reintroduced to treated women rendering current female treatment strategies inadequate.

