### Sample size

BV recurrence rates after recommended therapy are high. Sobel et al reported 50% recurrence within 3 months, and our group reported 52% recurrence within 6 months [8, 39]. We have chosen 12 weeks of follow up, as we believe this will be the optimal duration over which to measure the direct effect of treatment of the male partner on BV recurrence and minimises the risk of introduction of new untreated partners into the “treated partnership”. To obtain an estimate of the efficacy that we could expect from male partner treatment, we have used the reduction in risk reported from consistent condom use (50%) [8, 20] and male circumcision (40–60%) [31]. Based on our data we assume a 12-week BV recurrence rate in the control group of 40%, and conservatively estimate that treating male partners will reduce the risk of BV recurrence in females by 40%. This effect size is at the lower end of that reported from consistent condom use and circumcision.

Data indicate that women with an IUD in situ are more likely to experience BV recurrence [40, 41]. We hypothesise this is due to BV-organisms and biofilm persisting on the IUD after antimicrobial therapy. We will therefore limit recruitment of women with an IUD to no more than 20% of the total study population (68 women/couples), and this will be reviewed at the interim analysis.

With a total sample size of 290 heterosexual couples (145 per arm), we will have 80% power to detect a 40% reduction in BV recurrence from 40% in the control group to 24% in the intervention group (2-alpha = 5%). Assuming a 12-week loss to follow up of 15% in keeping with our previous trials, 342 couples will be recruited (171 couples per arm) to allow for a well-powered primary analysis.

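### The primary Cox model leaves out the factors used to stratify randomisation, which makes the test mildly conservative and gives up a little power if those factors are prognostic

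*Protocol article*

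**What the plan says.** The Allocation section of the protocol article describes 1:1 randomisation "in blocks of size four-six, will be used" with "stratification by recruitment site and known risk factors for recurrence: intrauterine device (IUD)-use and circumcision status". The prognostic claim is attached to IUD use and circumcision; site is listed separately.

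The article supports that claim elsewhere. Sample size states: "Data indicate that women with an IUD in situ are more likely to experience BV recurrence", and for that reason caps IUD users at 20% of the study population. Background and rationale describes "male circumcision prospectively associated with a significant reduction in BV-organisms and a reduction of BV in their female partners".

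Statistical methods fixes the main comparison: "Primary analyses will be simple unadjusted two-group comparisons of the randomised arms using Cox regression". It adds: "If there are important imbalances in baseline characteristics, further adjusted analyses will be performed". Planned subgroup analyses uses the strata, but only for subgroup comparisons and interaction tests. The Cox models for covariates associated with recurrence are aimed at predictors, not at the arm effect.

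**The concern.** Stratified blocks force the arms to be alike on the stratification factors. If those factors predict recurrence, part of the variation that an unadjusted model attributes to chance has been removed by design. The model standard error is then too large for the design actually run, the test rejects too seldom under the null, and some of the precision bought by stratifying is not used.

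The only route to adjustment in the text is observed imbalance. Blocking keeps IUD use, circumcision and site roughly balanced, so that route would rarely select the factors the protocol itself names as prognostic. At stake are some power and the coherence between design and analysis.

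**Working it through.** **Reproducing the plan's own figures.** From Sample size: 40% against 24%, two-sided 5%, 80% power, 145 per arm, 15% loss, 342 couples.

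- Without continuity correction, n = [1.96·√(2·0.32·0.68) + 0.842·√(0.40·0.60 + 0.24·0.76)]² / 0.16² = 132.3, so 133 per arm.
- With continuity correction, n = (132.3/4)·[1 + √(1 + 4/(132.3·0.16))]² ≈ 144.5, so 145 per arm. This matches.
- 290/0.85 = 341.2, so 342 couples. This matches.
- Under proportional hazards the implied marginal hazard ratio (HR) is ln(0.76)/ln(0.60) = 0.537.

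**Simulation.** From the protocol: 290 evaluable couples, 1:1 blocks of 4 and 6 within site × IUD × circumcision, IUD share at its 20% cap, and marginal 12-week risks of 40% in control and 24% in intervention under the alternative.

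My assumptions, not in the document:
- five sites holding 60/10/10/10/10% of couples;
- 65% of men uncircumcised;
- the same HR for IUD use and for an uncircumcised partner, set to 1, 1.5, 2 or 3;
- site log-HRs of 0, ±0.15, ±0.2 or ±0.3 respectively, with the large site at zero;
- exponential times, no dropout.

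The range for circumcision is plausible. Sample size cites a 40–60% reduction, which inverts to 1/0.6 = 1.7 up to 1/0.4 = 2.5. The article gives no effect size for the IUD. Each row rests on 3,000 trials under the null and 3,000 under the alternative. The adjusted model contains arm, IUD, circumcision and site.

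| Factor HR | Null, unadjusted: model SE / sampling SD | Type I error, unadjusted / adjusted | Power, unadjusted / adjusted | Average HR, unadjusted / adjusted |
|---|---|---|---|---|
| 1 | 0.1867 / 0.1888 | 5.3% / 5.6% | 82.0% / 82.4% | 0.541 / 0.537 |
| 1.5 | 0.1868 / 0.1839 | 4.0% / 4.5% | 83.8% / 84.4% | 0.533 / 0.525 |
| 2 | 0.1864 / 0.1795 | 4.3% / 5.6% | 84.8% / 87.2% | 0.534 / 0.517 |
| 3 | 0.1864 / 0.1725 | 3.6% / 5.0% | 86.7% / 91.5% | 0.532 / 0.492 |

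The Monte Carlo SE is about 0.4 points for type I error (√(0.05·0.95/3000)) and 0.5 to 0.7 points for each power figure.

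**Reading the table.**

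1. Excess of model SE over sampling SD: 0.1868/0.1839 = 1.016, 0.1864/0.1795 = 1.038, 0.1864/0.1725 = 1.081. That is about 2%, 4% and 8%. There is none when the factors have no effect.
2. Power gain from adjustment, from the unrounded results: 84.43 − 83.77 = 0.7 points, 87.20 − 84.77 = 2.4 points, 91.47 − 86.67 = 4.8 points. With no prognostic effect the difference is already 0.4 points, so the gain at HR 1.5 is negligible.
3. Log-HR interval under the alternative, adjusted against unadjusted model SE: 0.2176 against 0.2168, 0.2171 against 0.2160, 0.2181 against 0.2161. The adjusted interval is very slightly wider.
4. Adjusted calibration under the null, model SE against sampling SD: 0.1875 against 0.1895, 0.1873 against 0.1904, 0.1877 against 0.1916. The adjusted SE runs 1–2% low, which is close to nominal.

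**The case against.** The strongest reply is that the plan is valid as it stands and that most stronger criticisms fail. Taken in turn:

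- **A data-driven primary model.** A reader might infer that the imbalance clause leaves two candidate primary answers. The text does not say so: the primary model is fixed as unadjusted, and the adjusted analyses are described as further ones. What counts as important imbalance can properly be left to the analysis plan, which the article says will be written before any analysis.
- **Intervals that adjustment would shorten.** The simulation contradicts this. The unadjusted interval mildly over-covers, but the adjusted one is no narrower on the log scale.
- **A biased hazard ratio.** The unadjusted HR is nearer 1 because it is a marginal quantity. It is a different estimand, not an error, and the trial was sized on marginal risks of 40% and 24%.
- **Three known risk factors.** The article makes that claim for IUD use and circumcision only.
- **An underpowered trial.** Holding 0.537 fixed as the covariate-conditional HR, with factor HRs of 2.5 and 2.0, gives power of 80% unadjusted and 85% adjusted. But that setting implies an intervention risk of about 24.7–24.8%, a smaller effect than planned. With marginal risks held at 40% and 24%, unadjusted power does not fall as the factors strengthen.

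All five replies stand. They do not remove the point that the unadjusted choice is stated outright, not deferred, and sits badly with the article's own reason for stratifying.

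**Conclusion.** The point holds as a modest matter of efficiency and consistency. The protocol stratifies on factors of which two are said to predict recurrence, then specifies a main analysis that ignores all of them. If they are prognostic, the test is mildly conservative, with type I error of about 3.6% to 4.3% across the prognostic settings examined, and power is about 0.7 to 4.8 points lower than it could be. The upper figure needs HRs of 3 for both factors.

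The size rests on assumed factor effects, site structure and circumcision prevalence, and on no dropout. Any error works against finding an effect. A reader should not infer that the result would be invalid or the sample size too small: unadjusted power stayed above 80% in every setting with the planned marginal risks, and the 145 per arm and 342 couples reproduce.

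**What to change.** Make the primary analysis a Cox model adjusted for, or stratified by, IUD use, circumcision status and recruitment site. Pool small sites, or group them by the site types already named in Planned subgroup analyses. Report the unadjusted HR and the marginal 12-week recurrence risks by arm beside it. Choose covariates for any further adjusted analysis in advance on prognostic grounds, not on observed imbalance.

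The cost is wording in the protocol and the analysis plan. The three factors are entered in the database before allocation, so no new data are needed. There are two small downsides. The adjusted HR is a conditional estimand, which is why the marginal results should stand beside it. Sparse site strata need a pooling rule fixed before the data are seen. The simulation covers covariate adjustment; a fully stratified Cox model was not simulated.
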